## APPENDIX D. ACTIVITY SCHEDULE

The following table shows the required activities for this study. The individual activities are described in detail in the Operations Manual Section 3.

Study Activities Table

| Activity                               | Screening
(Day -21 to Day -1) | Cycle 1, Day 1 | Cycle 1, Days 2 - 5 | Cycle 1, Days 8, 15,
22 (± 1 day) | Cycle 1, Days 16 &
17 | Day 1 of Each Cycle
(± 1 day) | Days 8, 15, 22 of
Each Cycle (± 1 day) | Final Visit | 30-day F-U Visit
(± 7 days) | Post-Treatment
Follow-Up (every
3 months ± 7 days) |
|----------------------------------------|----------------------------------|----------------|---------------------|--------------------------------------|--------------------------|----------------------------------|-------------------------------------------|-------------|--------------------------------|----------------------------------------------------------|
| INTERVIEWS & QUESTIONNAIRES |                                  |                |                     |                                      |                          |                                  |                                           |             |                                |                                                          |
| Informed consent                       | ✓                                |                |                     |                                      |                          |                                  |                                           |             |                                |                                                          |
| Eligibility criteria                   | ✓                                | ✓              |                     |                                      |                          |                                  |                                           |             |                                |                                                          |
| Medical/oncology history               | ✓                                | ✓              |                     |                                      |                          |                                  |                                           |             |                                |                                                          |
| Adverse event assessment               | ✓                                | ✓              | ✓                   | ✓                                    | ✓                        | ✓                                | ✓                                         | ✓           | ✓                              |                                                          |
| Prior/concomitant therapy              | ✓                                | ✓              | ✓                   | ✓                                    | ✓                        | ✓                                | ✓                                         | ✓           | ✓                              |                                                          |
| LOCAL LABS & EXAMS          |                                  |                |                     |                                      |                          |                                  |                                           |             |                                |                                                          |
| Single 12-lead ECG                     | ✓                                |                |                     |                                      |                          |                                  |                                           | ✓           |                                |                                                          |
| Echocardiogram                         | ✓                                |                |                     |                                      |                          | ✓
C2 &
C6
only          |                                           |             |                                |                                                          |
| Cytogenetic Testing                    | ✓                                |                |                     |                                      |                          |                                  |                                           |             |                                |                                                          |
| Vital Signs                            | ✓                                | ✓              | ✓                   | ✓                                    |                          | ✓                                | ✓                                         | ✓           | ✓                              |                                                          |
| ECOG Performance Status                | ✓                                | ✓              |                     |                                      |                          | ✓                                |                                           | ✓           | ✓                              |                                                          |
| Targeted Physical Examination          | ✓                                | ✓              |                     |                                      |                          | ✓                                |                                           | ✓           | ✓                              |                                                          |
| Height (screening only) and Weight     | ✓                                | ✓              |                     |                                      |                          | ✓                                |                                           | ✓           | ✓                              |                                                          |
| TLS Prophylaxis                        |                                  | ✓              | ✓                   | ✓                                    |                          |                                  |                                           |             |                                |                                                          |
| TLS Chemistry Panel                    |                                  | ✓              | ✓
D2
only     | ✓                                    |                          |                                  |                                           |             |                                |                                                          |
| Urine Pregnancy test                   |                                  | ✓              |                     |                                      |                          | ✓                                |                                           | ✓           |                                |                                                          |
| Serum Pregnancy test                   | ✓                                |                |                     |                                      |                          |                                  |                                           |             |                                |                                                          |
| Viral serologies                       | ✓                                |                |                     |                                      |                          |                                  |                                           |             |                                |                                                          |
| Coagulation/Urinalysis                 | ✓                                |                |                     |                                      |                          |                                  |                                           | ✓           |                                |                                                          |
| CENTRAL LABS                    |                                  |                |                     |                                      |                          |                                  |                                           |             |                                |                                                          |
| Hematology/Chemistry                   | ✓                                | ✓              | ✓                   | ✓                                    |                          | ✓                                | ✓                                         | ✓           | ✓                              |                                                          |

| Activity                                                                    | Screening
(Day -21 to Day -1) | Cycle 1, Day 1 | Cycle 1, Days 2 - 5     | Cycle 1, Days 8, 15,
22 (± 1 day) | Cycle 1, Days 16 &
17 | Day 1 of Each Cycle
(± 1 day)         | Days 8, 15, 22 of
Each Cycle (± 1 day)   | Final Visit | 30-day F-U Visit
(± 7 days) | Post-Treatment
Follow-Up (every
3 months ± 7 days) |
|-----------------------------------------------------------------------------|----------------------------------|----------------|-------------------------|--------------------------------------|--------------------------|------------------------------------------|---------------------------------------------|-------------|--------------------------------|----------------------------------------------------------|
| Triplicate ECG                                                              |                                  | ✓              | ✓
D2
only         | ✓ D15
only                        | ✓ D16
only            |                                          |                                             |             |                                |                                                          |
| Creatine phosphokinase and
troponin                                      |                                  | ✓              | ✓
D2 &
D3
only | ✓
D15
only                     | ✓                        | ✓
C2 –
C8
only                  | ✓
D15 of
C2,
C4,
C6, C8
only |             |                                |                                                          |
| Serum β2 microglobulin                                                      | ✓                                |                |                         |                                      |                          |                                          |                                             |             |                                |                                                          |
| ABBV-467 Blood PK Samples                                                   |                                  | ✓              | ✓
D2 &
D3
only | ✓
D15
only                     | ✓                        | ✓
C2,
C4,
C6, C8
only        |                                             |             |                                |                                                          |
| AML subjects (expansion only):
ABBV-467 Urine PK Samples                 |                                  | ✓              | ✓
D2 &
D3
only |                                      |                          |                                          |                                             |             |                                |                                                          |
| Peripheral Blood biomarker samples                                          | ✓                                | ✓              | ✓
D2
only         |                                      | ✓
D16
only         | ✓
C2, C3,
C4;
every
3 cycles |                                             | ✓           |                                |                                                          |
| AML subjects: Bone marrow
aspirate and biopsy for biomarker
research  | ✓                                |                |                         |                                      |                          | C2, then
every
3 cycles            |                                             | ✓           |                                |                                                          |
| MM subjects: Bone marrow
aspirate and biopsy for biomarker
research   | ✓                                |                |                         |                                      |                          | ✓
C5
only                          |                                             | ✓           |                                |                                                          |
| Optional biomarker samples (DNA
and RNA) (taken if consent given)        |                                  | ✓              |                         |                                      |                          | ✓
C3
only                          |                                             | ✓           |                                |                                                          |
| DISEASE ASSESSMENT                                                   |                                  |                |                         |                                      |                          |                                          |                                             |             |                                |                                                          |
| AML subjects: Bone Marrow
Aspirate and Biopsy for Response
Assessment | ✓                                | ✓              |                         |                                      |                          | C2, then
every
3 cycles            |                                             | ✓           |                                |                                                          |
| AML subjects: Response
Assessment                                        |                                  |                |                         |                                      |                          | C2, then
every
3 cycles            |                                             | ✓           |                                |                                                          |
| MM Subjects: Serum protein
immunofixation                                | ✓                                | ✓              |                         |                                      |                          | ✓                                        |                                             | ✓           |                                |                                                          |
| MM Subjects: Serum protein
electrophoresis                               | ✓                                | ✓              |                         |                                      |                          | ✓                                        |                                             | ✓           |                                |                                                          |

| Activity                                                     | Screening
(Day -21 to Day -1) | Cycle 1, Day 1          | Cycle 1, Days 2 - 5 | Cycle 1, Days 8, 15,
22 (± 1 day) | Cycle 1, Days 16 &
17 | Day 1 of Each Cycle
(± 1 day) | Days 8, 15, 22 of
Each Cycle (± 1 day) | Final Visit | 30-day F-U Visit
(± 7 days) | Post-Treatment
Follow-Up (every
3 months ± 7 days) |
|--------------------------------------------------------------|----------------------------------|-------------------------|---------------------|--------------------------------------|--------------------------|----------------------------------|-------------------------------------------|-------------|--------------------------------|----------------------------------------------------------|
| MM Subjects: Serum quantitative immunoglobulins              | ✓                                | ✓                       |                     |                                      |                          | ✓                                |                                           | ✓           |                                |                                                          |
| MM Subjects: Serum free light chains                         | ✓                                | ✓                       |                     |                                      |                          | ✓                                |                                           | ✓           |                                |                                                          |
| MM Subjects: Urine protein immunofixation                    | ✓                                | ✓                       |                     |                                      |                          | ✓                                |                                           | ✓           |                                |                                                          |
| MM Subjects: Urine protein electrophoresis                   | ✓                                | ✓                       |                     |                                      |                          | ✓                                |                                           | ✓           |                                |                                                          |
| MM Subjects: Skeletal survey/
Assessment of lytic disease | ✓                                | As clinically indicated |                     |                                      |                          |                                  |                                           |             |                                |                                                          |
| MM Subjects: Plasmacytoma evaluation                         | ✓                                | As clinically indicated |                     |                                      |                          |                                  |                                           |             |                                |                                                          |
| MM Subjects: Bone marrow aspirate for response assessment    | ✓                                | ✓                       |                     |                                      |                          | ✓                                |                                           | ✓           |                                |                                                          |
| MM Subjects: Bone marrow core biopsy for response assessment | ✓                                |                         |                     |                                      |                          |                                  |                                           |             |                                |                                                          |
| MM subjects: Response assessment                             |                                  |                         |                     |                                      |                          | ✓                                |                                           | ✓           |                                |                                                          |
| Disease Status                                               |                                  |                         |                     |                                      |                          |                                  |                                           |             | ✓                              | ✓                                                        |
| Survival status                                              |                                  |                         |                     |                                      |                          |                                  |                                           |             | ✓                              | ✓                                                        |
| Subsequent anticancer therapy                                |                                  |                         |                     |                                      |                          |                                  |                                           |             | ✓                              | ✓                                                        |
| Rx TREATMENT                                          |                                  |                         |                     |                                      |                          |                                  |                                           |             |                                |                                                          |
| Hospitalization/Inpatient Monitoring (Dose Escalation Only)  |                                  | ✓                       | ✓
D2 Only        | ✓
D8 Only                         |                          |                                  |                                           |             |                                |                                                          |
| Administer ABBV-467
(Once weekly for every 28-day cycle)  |                                  | ✓                       |                     | ✓                                    |                          | ✓                                | ✓                                         |             |                                |                                                          |

AML = acute myeloid leukemia; C = Cycle; D = Day; ECG = electrocardiogram; ECOG = Eastern Cooperative Oncology Group; F-U = Follow-Up; MM = multiple myeloma; PK = pharmacokinetic; TLS = tumor lysis syndrome

## APPENDIX E. DEFINITION OF LINES OF THERAPY (MULTIPLE MYELOMA ONLY)

According to the IMWG Consensus panel on uniform reporting criteria in clinical trial, A line of therapy is defined as 1 or more cycles of a planned treatment regimen. This may consist of 1 or more planned cycles of single-agent therapy or combination therapy, as well as a sequence of treatments administered in a planned manner. For example, a planned induction, followed by autologous stem cell transplantation, followed by maintenance is considered 1 line of therapy. A new line of therapy starts when a planned course of therapy is modified to include other treatment agents (alone or in combination) as a result of disease progression, relapse or toxicity, or when a planned period of observation is interrupted by the need for additional treatment for the disease. Modification of drug doses or resuming therapy after holding will not be considered a new line of therapy provided that there was no evidence of disease progression per IMWG response criteria.

## APPENDIX F. DEFINITIONS OF LABORATORY AND CLINICAL TUMOR LYSIS SYNDROME

| Metabolic Abnormality            | Criteria for Classification of Laboratory Tumor Lysis Syndrome                                        | Criteria for Classification of Clinical Tumor Lysis Syndrome                                                                                                                                                                                                                     |
|----------------------------------|-------------------------------------------------------------------------------------------------------|----------------------------------------------------------------------------------------------------------------------------------------------------------------------------------------------------------------------------------------------------------------------------------|
| Hyperuricemia                    | Uric acid > 8.0 mg/dL (475.8 µmol/L)                                                                  | Not applicable                                                                                                                                                                                                                                                                   |
| Hyperphosphatemia                | Phosphorus > 4.5 mg/dL (1.5 mmol/L)                                                                   | Not applicable                                                                                                                                                                                                                                                                   |
| Hyperkalemia                     | Potassium > 6.0 mmol/L                                                                                | Cardiac dysrhythmia or sudden death probably or definitely caused by hyperkalemia                                                                                                                                                                                                |
| Hypocalcemia                     | Corrected calcium < 7.0 mg/dL (1.75 mmol/L) or ionized calcium < 1.12 mg/dL (0.3 mmol/L) a | Cardiac dysrhythmia, sudden death, seizure, neuromuscular irritability (tetany, paresthesias, muscle twitching, carpopedal spasm, Trousseau's sign, Chvostek's sign, laryngospasm, or bronchospasm), hypotension, or heart failure probably or definitely caused by hypocalcemia |
| Acute kidney injury b | Not applicable                                                                                        | Increase in the serum creatinine level of 0.3 mg/dL (26.5 µmol/L) or the presence of oliguria, defined as an average urine output < 0.5 mL/kg/hr for 6 hours                                                                                                                     |

TLS = tumor lysis syndrome

a. The corrected calcium level in mg/dL = measured calcium level in mg/dL + 0.8 × (4-albumin in g/dL).

b. Acute kidney injury, unless attributable to another cause, represents clinical TLS even if criteria for laboratory TLS are not satisfied.

Note: In laboratory TLS, 2 or more metabolic abnormalities must be present during the same 24-hour period within 3 days before the start of therapy or up to 7 days afterward. Not directly or probably attributable to therapeutic agent.

Note: Clinical TLS requires the presence of Laboratory TLS plus 1 or more findings from the Clinical TLS column.

Source: Howard et al, 2011

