**Table 2. Proposed Dose Levels**

| Dose Level   | 1    | 2    | 3    |  |  |  |  |  |  |  |  |
|--------------|------|------|------|--|--|--|--|--|--|--|--|
| Dose (mg/kg) | 0.16 | 0.32 | 0.53 |  |  |  |  |  |  |  |  |

Throughout all parts of the study, ABBV-467 will be administered with an abbreviated dose ramp-up, in which 50% of the target dose will be administered on Cycle 1 Day 1 (C1D1), and full target dose thereafter (weekly until disease progression, unacceptable toxicity, or withdrawal of consent).

For each dose level, the second subject will not be dosed until at least 48 hours have elapsed since the initial dose for the first subject at that dose level.

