## Tumor Lysis Syndrome

Subjects with MM with high tumor burden (e.g., high bone marrow plasma cell infiltration, plasma cell leukemia, or bulky plasmacytomas), rapidly increasing M-protein or light chains or high proliferative activity, plasmablastic morphology, or compromised renal function ( $CrCl < 50$  mL/minute) may be at higher risk of developing TLS. There is a potential risk for TLS in subjects with AML, especially in those with elevated leukocyte count, circulating blasts, elevated pretreatment lactate dehydrogenase levels, renal dysfunction, and dehydration. To mitigate the risk for TLS all subjects enrolled into the study will need TLS prophylaxis and monitoring. For subjects at higher risk for TLS, additional mitigation measures with more intensive laboratory monitoring and intervention should be implemented. Prophylactic reductions of potassium, inorganic phosphorus or uric acid above normal range are recommended prior to beginning study treatment and to be continued based on the ongoing risk of TLS. Please reference [Appendix F](#) for additional information on the evidence of TLS and [Appendix G](#) for initial management of electrolyte abnormalities and prevention of TLS.

During dose escalation, each subject should be hospitalized the night prior to C1D1 for hydration, treatment with uric acid-reducing agents, and monitoring. Tumor lysis syndrome laboratories will be obtained at 3 different time points: immediately prior to the first dose, 6 to 8 hours after the first dose, and approximately 24 hours after the first dose (on C1D2).

The subject may be discharged once the laboratory results on C1D2 are reviewed (approximately 24 hours after first dose) and confirm the absence of TLS. If discharged since first dose, subjects will be re-hospitalized the night prior to C1D8 for hydration, treatment with uric acid-reducing agents, and monitoring.

Tumor lysis syndrome prophylaxis and management for the second dose of ABBV-467 will be managed in the same manner as the first dose described above. Subjects who experience clinical or laboratory TLS, or other significant toxicity following the first or second dose of ABBV-467 should discuss the safety monitoring plan for subsequent doses of ABBV-467 with the AbbVie TA MD.

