**Table 8. TLS Chemistry Panel Sampling Times**

| Cycle 1 Day 1                                                            | Cycle 1 Day 8                                                            | Cycle 1 Days 15 & 22 |
|--------------------------------------------------------------------------|--------------------------------------------------------------------------|----------------------|
| 0 (pre-infusion)
6 – 8 hours post EOI
24 hours post-EOI (on Day 2) | 0 (pre-infusion)
6 – 8 hours post EOI
24 hours post-EOI (on Day 9) | 0 (pre-infusion)     |

EOI = end of infusion

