### 3.17 Hospitalization/Inpatient Monitoring

---

During dose escalation, each subject should be hospitalized the nights prior to C1D1 and C1D8 for hydration, treatment with uric acid-reducing agents, and monitoring. The subject may be discharged once TLS labs are reviewed 24 hours after dosing. See Protocol Section 6.2 for further detail.

Subjects in Japan will be hospitalized for the duration of the DLT period (see Section 5.1).

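### The Appendix F window for laboratory TLS closes on Day 8, so TLS first seen on the Day 9 panel after the first full dose does not meet the definition, except as acute kidney injury

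*Protocol*

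**What the plan says.** Appendix F defines laboratory TLS as two or more metabolic abnormalities in one 24-hour period, occurring "within 3 days before the start of therapy or up to 7 days afterward". It adds that "Clinical TLS requires the presence of Laboratory TLS plus 1 or more findings from the Clinical TLS column", with one exception in footnote b: "Acute kidney injury, unless attributable to another cause, represents clinical TLS even if criteria for laboratory TLS are not satisfied".

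The dosing schedule is in Section 4.1, under Table 2: "50% of the target dose will be administered on Cycle 1 Day 1 (C1D1), and full target dose thereafter". Dosing is weekly, so the first full dose is C1D8.

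The rest of the protocol treats both doses as TLS-risk events:

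- Operations Manual Section 3.17 says that in dose escalation "each subject should be hospitalized the nights prior to C1D1 and C1D8 for hydration".
- Operations Manual Table 8 schedules TLS panels around C1D8 before infusion, 6–8 hours after the end of infusion, and 24 hours after it, on Day 9.
- Section 6.2 states: "Tumor lysis syndrome prophylaxis and management for the second dose of ABBV-467 will be managed in the same manner as the first dose". It asks for a discussion of the monitoring plan for subjects with "clinical or laboratory TLS, or other significant toxicity following the first or second dose of ABBV-467". It also makes the Appendix F criteria the trigger for TLS management and for holding doses.
- Section 5.4 requires a TLS risk-reducing agent through Day 15 of Cycle 1.

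**The concern.** A window anchored to a single start of therapy fits a regimen whose first dose is the full dose. Here the first dose is half strength, and the definition expires on the day the full dose is given. The last post-dose panel scheduled to detect TLS after that dose can return two qualifying abnormalities that, read literally, are not laboratory TLS. Hyperkalemic arrhythmia or hypocalcemic seizure on that day would then not be clinical TLS either.

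At stake is how an anticipated risk is labelled and recorded in a first-in-human study whose first primary objective is to characterize safety. The label bears on the Tumor Lysis Syndrome eCRF, which Section 6.1 ties to Section 6.2, and on the Section 6.2 triggers worded in terms of TLS. Sites that apply Appendix F literally and sites that read it loosely would report the same event differently.

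**Working it through.** The protocol states no figure to reproduce; the check is day arithmetic.

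**Inputs**

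- Start of therapy: C1D1, taken as 0 h (Section 4.1).
- Window closes 7 days (168 h) after the start (Appendix F).
- Post-dose panels for C1D8: 6–8 h and 24 h after end of infusion (Operations Manual Table 8).
- Visit window for Cycle 1 Day 8: ±1 day (Appendix D).
- Assumptions: 0.5 h infusion (the Section 5.7 minimum), the same clock time each week, and the 6–8 h panel drawn on the dosing day.

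**Formulas**

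- Elapsed hours = 24 × (dose day − 1) + 0.5 + hours after end of infusion.
- Calendar offset = study day of the panel − 1.

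**Results**

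| C1D8 dose given on | Panel | Elapsed | Calendar offset | Inside by calendar day? | Inside by elapsed time? |
|---|---|---|---|---|---|
| Day 7 | 6–8 h | 150.5–152.5 h (6.27–6.35 d) | +6 | yes | yes |
| Day 7 | 24 h | 168.5 h (7.02 d) | +7 | yes | no, by 0.5 h |
| Day 8 (nominal) | 6–8 h | 174.5–176.5 h (7.27–7.35 d) | +7 | yes | no |
| Day 8 (nominal) | 24 h | 192.5 h (8.02 d) | +8 | **no** | **no** |
| Day 9 | 6–8 h | 198.5–200.5 h (8.27–8.35 d) | +8 | no | no |
| Day 9 | 24 h | 216.5 h (9.02 d) | +9 | no | no |

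By calendar day, the post-dose panels outside the window number 1 of 2 on the nominal schedule, 2 of 2 with the dose on Day 9, and 0 of 2 with the dose on Day 7. The nominal 24 h panel is outside on either way of counting.

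**The cutoff also splits a natural pair.** The two post-dose panels lie 24 − 8 = 16 h to 24 − 6 = 18 h apart, so one abnormality on each could meet the same-24-hour rule. With the second panel outside the window, the pair does not qualify.

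**Does Appendix G cover the gap?** Not entirely, because its thresholds differ. Appendix F counts phosphorus above 4.5 mg/dL and corrected calcium below 7.0 mg/dL. Appendix G acts on phosphorus of at least 5.0 mg/dL with a rise of at least 0.5 mg/dL, and on calcium of 7.0 mg/dL or less only if the subject is symptomatic. As an illustration, Day 9 values of phosphorus 4.8 and asymptomatic corrected calcium 6.8 would be two Appendix F abnormalities but would meet neither Appendix G criterion. Such a pair is caught only if the Appendix F window covers it.

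**With the window re-anchored.** Day 8 + 7 = Day 15. After the first full dose and up to the next dose, Table 8 has three panels: 6–8 h, 24 h, and Day 15 pre-infusion. By calendar day the present window covers 1 of 3 and the re-anchored window 3 of 3.

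**The case against.** The strongest reply is that little follows from the label. Section 7.5 tabulates adverse events by MedDRA term, and no endpoint or analysis uses the Appendix F classification. Section 6.2 calls for abnormal chemistry to be corrected promptly and for monitoring throughout treatment. Appendix G holds dosing on a single laboratory criterion with no 7-day limit. Grade 4 non-hematologic laboratory abnormalities are DLTs whatever they are called. Other significant toxicity also triggers the monitoring discussion. All of this stands and is why the point is minor. It does not close the gap, since Section 6.2 uses Appendix F as a criterion and Appendix G's thresholds are not the same.

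The size also needs qualifying. Table 8 ties its panels to the hospital stays, which Appendix D confines to dose escalation. In expansion the Section 6.2 minimum is pre-dose and 6–8 h, which is Day 8 and inside by calendar day. The Day 9 dosing case rests on Appendix D's ±1 day, whereas Section 5.7 allows one-day scheduling delays only after Cycle 1. The Day 15 sample is also the pre-dose sample for the third infusion. These points limit the variants; the nominal Day 9 exclusion is unaffected.

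It can also be said that Appendix F adapts a cited published definition, or that the start of therapy may be read as each dose. The text does not say the latter. Section 6.2 names the second dose and Appendix G names dose escalation where a later step is meant; Appendix F does neither. The cited source was not consulted.

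**Conclusion.** The point holds as wrong as written, at minor severity. On the nominal schedule the Day 9 panel after the first full dose lies outside the laboratory-TLS window, whether counted by calendar day or by elapsed time. Clinical TLS resting on that panel is excluded too, with acute kidney injury the only exception.

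This rests on taking C1D1 as the start of therapy, as the text reads, and on the infusion timing assumed above. The day count is firm. How often TLS would first appear between the Day 8 and Day 9 panels cannot be estimated from the document. The consequence is confined to classification and reporting of TLS and to the Section 6.2 triggers worded in those terms. The monitoring discussion is at risk only for events, such as asymptomatic laboratory TLS, that a site does not regard as significant toxicity. No effect on DLT assessment or dose selection is shown.

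**What to change.** In Appendix F, run the window from 3 days before C1D1 to 7 days after each of the first two doses (C1D1 and C1D8). It then ends at about Day 15, matching the prophylaxis period in Section 5.4. State that days are calendar days, so that panels drawn on the closing day are not in doubt.

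As a secondary wording repair in Appendix G, let the first-24-hour rules name both C1D1 and C1D8; at present they name only the first dose. Complete the unfinished sentence at the start of the ongoing-dosing section in the same way. Section 6.2 already manages the second dose like the first, so this only aligns the text.

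The cost is wording in two appendices, with no new samples, prophylaxis or hospital stay.
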